## Abstract

**Background:**

Worldwide, type 2 diabetes (T2DM) prevalence has more than doubled over two decades. In Australia, diabetes is the second highest contributor to the burden of disease. Lifestyle modification programs comprising diet changes, weight loss and moderate physical activity, have been proven to reduce the incidence of T2DM in high risk individuals.

As part of the Council of Australia Governments, the State of Victoria committed to develop and support the diabetes prevention program *‘Life! Taking action on diabetes’* (Life!) which has direct lineage from effective clinical and implementation trials from Finland and Australia. The Melbourne Diabetes Prevention Study (MDPS) has been set up to evaluate the effectiveness and cost-effectiveness of a specific version of the Life! program.

**Methods/design:**

We intend to recruit 796 participants for this open randomized clinical trial; 398 will be allocated to the intervention arm and 398 to the usual care arm. Several methods of recruitment will be used in order to maximize the number of participants. Individuals aged 50 to 75 years will be screened with a risk tool (AUSDRISK) to detect those at high risk of developing T2DM. Those with existing diabetes will be excluded. Intervention participants will undergo anthropometric and laboratory tests, and comprehensive surveys at baseline, following the fourth group session (approximately three months after the commencement of the intervention) and 12 months after commencement of the intervention, while control participants will undergo testing at baseline and 12 months only.

The intervention consists of an initial individual session followed by a series of five structured-group sessions. The first four group sessions will be carried out at two week intervals and the fifth session will occur eight months after the first group session. The intervention is based on the Health Action Process Approach (HAPA) model and sessions will empower and enable the participants to follow the five goals of the Life! program.

**Discussion:**

This study will determine whether the effect of this intervention is larger than the effect of usual care in reducing central obesity and cardiovascular risk factors and thus the risk of developing diabetes and cardiovascular disease. Also it will evaluate how these two options compare economically.

**Trial registration:**

Australian New Zealand Clinical Trials Registry ACTRN12609000507280

## Background

The dramatic increase in the prevalence of type 2 diabetes (T2DM) is posing a major international health problem
[1] and there is an urgent need to implement a widespread and coordinated approach to its prevention. Worldwide, T2DM prevalence has more than doubled since 1981 and the total number of cases was almost 347 million adults in 2010
[2]. Currently in Australia, diabetes is the second highest contributor to the burden of disease, responsible for 5.2% of disability adjusted life-years (DALYs), and by 2023 it will be the leading cause, responsible for 8.6% of the overall disease burden
[3]. Diabetes also poses an enormous economic burden, accounting for AU$1.4 billion in 2003 and projected to increase to almost AU$7 billion by 2033
[4].

Several recent clinical trials conducted on individuals have demonstrated that lifestyle modification with weight loss and moderate exercise can reduce the incidence of T2DM in high risk individuals by up to 58%
[5-7]. Lifestyle modification has been shown to be even more effective than drug treatment using metformin or rosiglitazone
[5,8] and seems to have an impact lasting at least several years following the active intervention
[9-11]. The challenge is to implement the outcomes of these studies in the ‘real world’ of financially constrained health services.

In 2004 to 2006, the Australian Government funded a group-based lifestyle modification implementation trial - the Greater Green Triangle Diabetes Prevention Project (GGT DPP) - to determine its efficacy and feasibility in primary care
[12]. From changes in waist circumference, it is imputed that this program reduced participants’ projected risk of diabetes by 40%, cardiovascular disease (CVD) by 16%. GGT DPP was derived from the Finnish Diabetes Prevention Study (DPS) clinical trial
[13] and a sister project to the Good Ageing in Lahti Region (GOAL) Lifestyle Implementation Trial in Finland
[14].

### Life! taking action on diabetes (Life!)

In Australia, the Federal and State Governments collaborate through the Council of Australian Governments (COAG). In health, diabetes prevention is considered one of the top priority areas. In 2007, as part of the COAG initiative for diabetes, the Victorian State Government committed AU$18.3 million of funding over four years for 25,000 high-risk individuals over 50 years old to participate in a diabetes prevention program called *‘Life! Taking action on diabetes’* (Life!) to be conducted by Diabetes Australia Victoria (DA Vic). Life! is a group based lifestyle change program and has direct lineage from the DPS, GOAL, and GGT DPP and its goals are described below.

The first Life! participants started the six session program in April 2008. At the start of June 2012, 13,946 people had commenced a Life! group course. In 2010, the Life! program underwent some changes to the entry requirements and intervention structure. The program will continue to evolve over time. In May 2011, the Victorian State Government announced continued funding for Life! for a further four years with an added emphasis on CVD prevention. The Life! program was originally accessible for individuals 50 years old and over with good English proficiency and at high risk of developing diabetes.

The goals of the Life! program were developed based on the experiences reported by two clinical trials of prevention of T2DM with life-style modification
[5,6]. The intervention goals are: (1) no more than 30% energy from fat; (2) no more than 10% energy from saturated fat; (3) at least 15 g/1,000 kcal fiber intake; (4) at least 30 minutes/day moderate intensity physical activity; and (5) at least 5% reduction in body weight. Participants individually tailor and modify the goals over the course of the sessions.

### The Melbourne diabetes prevention study (MDPS)

The Melbourne Diabetes Prevention Study (MDPS) is a research project set up to study in detail a cohort of individuals undertaking the Life! program in order to evaluate the effectiveness of a large-scale prevention program and, importantly, the cost-effectiveness. The focus of the present study is a specific modification of the program developed in 2011. The program to be evaluated consists of an individual session and five group sessions (‘1+5 model’) as presented further below.

The working hypotheses of the MDPS are that (1) the MDPS program results in statistically and clinically significant changes (relative to usual care) in clinical, behavioral, and patient relevant outcomes, particularly changes in weight and waist circumference, that reduce the risk of progression to T2DM; and (2) the diabetes prevention program provided in this study is both ‘cost-effective’ (relative to usual care using a yardstick of $50,000 per quality adjusted life year (QALY)) and performs well in the second stage filter implementation analysis (the protocol for the economic appraisal will be presented separately).

## Methods/design

### Study design

The MDPS is a prospective, open, randomized controlled trial to assess the effectiveness and cost-effectiveness of a structured diabetes prevention program implemented in Victoria for people 50- to 75-years old who are at high risk of developing T2DM. This is a parallel group study, with the intervention group receiving a diabetes prevention program for 12 months and the control group receiving usual care from their General Practitioners (GPs) during the same time period. Intervention participants will undergo anthropometric and laboratory tests, and comprehensive surveys at baseline, following the fourth group session (approximately three months after the commencement of the intervention) and 12 months after commencement of the intervention, while control participants will undergo testing at baseline and 12 months only.

The study is coordinated from the Melbourne metropolitan campus of Deakin University (Victoria, Australia) and is supported by the National Health and Medical Research Council of Australia (NH&MRC). Ethical approval was obtained from the Deakin University Human Research Ethics Committee (EC66-2009). Written informed consent will be obtained from all participants.

MDPS uses the existing infrastructure and accredited Life! providers set in place by DA Vic. Deakin University is one of the accredited Life! providers. Life! facilitators will undergo additional training because the MDPS intervention is a ‘1+5 model’ version of the Life! program.

### Participants

The study population is comprised of individuals 50- to 75-years old, living in the Melbourne metropolitan area, who are at risk of developing diabetes, but currently do not have diabetes.

### Recruitment processes

Participants are recruited as described below from general practices, by accredited Life! facilitators, in pharmacies, and also at local community events within the study catchment. The project coordinator provides recruiters with specific training to ensure standardized recruitment procedures.

1) Recruitment through general practices

Patients 50- to 75-years old are invited to complete the Australian Diabetes Risk Assessment tool (AUSDRISK). Those who score 15 or more are referred to the study by their General Practitioner or Practice Nurse.

2) Recruitment through accredited Life! providers

A Life! provider is an organization accredited to deliver the Life! program. These organizations and DA Vic have the opportunity to refer individuals into MDPS.

3) Recruitment through pharmacies

MDPS project pharmacists and research assistants visit pharmacies and target screening to patients 50-years old and older who have easily-identifiable characteristics (such as high body mass index or blood pressure) that are suggestive of higher risk of T2DM. The questionnaire is completed in the pharmacy along with the individual’s details.

4) Recruitment through community organization or event

Recruitment also takes place in community settings such as health clubs/gymnasiums, local chapters of community service organizations (for example, Rotary, Lions Club and so on) and community fetes and expos.

### Eligibility

Individuals 50-to 75-years old are asked to complete an AUSDRISK test
[15] that identifies individuals at high risk of developing T2DM within five years. Approximately one person in every seven with a score over 15 will develop diabetes within five years. The ten-item self-report AUSDRISK test is comparable with the Finnish Diabetes Risk Score (FINDRISC) tool
[16], but includes ethnicity and country of birth appropriate for the multicultural Australian population.

The procedure for screening, eligibility and recruitment can be viewed in Figure 
1. A score of 15 or more on the AUSDRISK test
[17] is the primary inclusion criterion. If the score is 15 or above, the MDPS team member will assess the eligibility of the individual by checking the exclusion criteria, which for both males and females are (1) already on treatment for type 1 or type 2 diabetes; (2) laboratory evidence of existing T2DM defined as having a two-hour oral glucose tolerance test (OGTT) result of greater than or equal to 11.1 mmol/L and/or a fasting blood glucose greater than or equal to 7 mmol/L; (3) cancer (not in remission); (4) severe mental illness; (5) substance abuse; (6) myocardial infarction in the last three months; (7) pregnancy; (8) difficulty with English and (9) other household members involved in the study.

**Figure 1 F1:**
[figure not shown]
Flow chart of the MDPS.

### Consent

The MDPS project coordinator contacts eligible participants to discuss the study, confirm eligibility criteria and arrange baseline testing. Eligible individuals recruited through the above strategies are provided with a plain language statement and consent form approved by the Ethics Committee at the time of recruitment.

### Intervention

The MDPS intervention consists of an initial individual session followed by a series of five structured group sessions. The initial individual session forms a specific design component of the intervention to maximize participant retention and increase their personal risk awareness. The delivery of an individual session runs in accordance with trials that have indicated that lifestyle interventions that incorporate individual feedback and goal setting foster a greater sense of participant engagement, motivation and ability to maintain lifestyle changes in the long term
[11]. The individual session will be 30 to 45 minutes in duration, involving the participant and the facilitator only, and encompassing risk perception, goal setting, and motivation to change.

Four group sessions are provided at two week intervals. A fifth and final group session occurs eight months after the first group session. All sessions are led by a trained Life! facilitator, with generally 8 to 15 participants in each group. The duration of each group session is approximately 1.5 hours. The control group continues with usual care as provided by their GP. They may be offered a diabetes prevention program at the end of the study.

The intervention and data collection time points for both intervention and usual care groups are shown in Figure 
2.

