**Figure 2 F2:**
[figure not shown]
**Structure of the MDPS Group Program.** IS: Individual session.S1-S5: group sessions.T1, T2, T3: anthropometric and laboratory tests.

The theoretical framework of this intervention is based on the Health Action Process Approach (HAPA) model and self-regulation theory
[18-20]. Several other theories, strategies and constructs are incorporated into the design of the intervention. These include the social learning theory, the trans-theoretical theory of stages of change
[21,22], empowerment-oriented counseling
[23-25], goal-setting approach
[26,27], self-efficacy and self-evaluation
[18,28].

The group sessions follow the structure of the HAPA model. Each session is structured with a major emphasis on creating an interactive and socially-supportive atmosphere. In these sessions the facilitator enables goal setting, moderates the discussion and feedback, and strengthens the role of the group as a source of social support. In addition, individual feedback is provided to participants from anthropometric and laboratory measurements at the second clinical testing session (which follows the fourth group session - approximately three months after the commencement of the intervention). This individual feedback is used to evaluate the impact of the intervention and to sustain participants’ motivation in their lifestyle changes.

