### Sample size and power calculation

For the estimation of sample size for two groups, with a two-sided 5% significance level and 80% power, the total number required will be 598 (299 in each arm). The sample size calculation was based on the observed mean change in diastolic blood pressure, a CVD risk factor, in the GGT-DPP and powered to detect an effect size of at least 0.23. To allow for an estimated attrition of up to 25% (estimate based on the GGT DPP), we require a total sample of 796 (398 in each arm). This sample size will provide sufficient power for other CVD risk factors, such as total and high-density lipoprotein (HDL)-cholesterol, as well as diabetes risk factors including fasting plasma glucose, weight, and waist circumference, as these are all expected to have larger effect sizes.

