### Data analysis

Analyses will be performed using Stata version 12 or later, and the ‘intention-to-treat’ principle will be adhered to. Baseline characteristics will be compared between intervention and control groups using chi-square tests, independent t-tests, and the Wilcoxon rank-sum test as appropriate. Primary and secondary outcomes (as described above) will be evaluated using mixed models, treating ‘group’ as a between-subject factor and ‘time’ as a within-subject factor. Two-sided tests will be used, with a level of *P* <0.05 determining statistical significance.

A separate and parallel economic evaluation protocol will be described elsewhere.

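### The intervention is delivered in session groups, but neither the sample size nor the stated model allows for clustering; if outcomes within groups correlate, the standard error is understated and 80% power for a 0.23 effect is not delivered

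*Protocol article*

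**What the plan says.** The Intervention section describes one individual session followed by five group sessions: "All sessions are led by a trained Life! facilitator, with generally 8 to 15 participants in each group". Controls stay with their GP's usual care, so they belong to no session group. The text below Figure 2 makes group influence part of the method: the facilitator "strengthens the role of the group as a source of social support".

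The section on sample size and power states that, "with a two-sided 5% significance level and 80% power", "the total number required will be 598 (299 in each arm"). The calculation was "powered to detect an effect size of at least 0.23", based on the change in diastolic blood pressure in the earlier Australian implementation trial. Attrition of up to 25% raises the total to 796 (398 per arm). No ICC or design effect appears.

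The Data analysis section specifies mixed models, "treating ‘group’ as a between-subject factor and ‘time’ as a within-subject factor". In that sentence the between-subject factor is the trial arm, since the sentence before it compares baseline characteristics of the intervention and control arms. No term for session group or facilitator is named.

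**The concern.** This is a partially nested design. Intervention participants share sessions, a facilitator and each other's support, while controls share none of these. A programme that relies on members influencing one another gives reason to expect their outcomes to be correlated.

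A positive correlation makes the mean of the intervention arm more variable than the same number of independent people would give. A model with only arm, time and repeated measures within person does not see that extra variance. Confidence intervals for the arm difference would then be too narrow, and the sample size would be too small for its stated power. The error leans towards declaring a difference, in a trial whose results are meant to inform policy.

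**Working it through.** **Inputs from the article.** Two-sided alpha 0.05; power 80%; standardised effect 0.23 (so SD = 1); 299 analysed per arm; attrition 25%; session groups of 8 to 15, midpoint 11.5.

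**Assumptions.** ICC 0.01, 0.02 and 0.05, since the article gives none. Total variance is taken as 1 in both arms, attrition as evenly spread over groups, and group sizes as equal.

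**Step 1: the plan's own figure.** For independent individuals, n per arm = 2 × (1.960 + 0.8416)² / 0.23² = 296.7, so 297; a t-based version gives 298. The stated 299 is reproduced to within two. With 299 per arm the standard error is √(2/299) = 0.0818, and power = Φ(0.23/0.0818 − 1.96) = Φ(0.852) = 80.3%. For attrition, 299/0.75 = 398.7, against the stated 398. So the figure carries no allowance for clustering.

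**Step 2: analysed group size.** The 299 is a number after attrition, so the group size must be too: 11.5 × 0.75 ≈ 8.6 (range 6 to about 11).

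**Step 3: clustering in the intervention arm only.**
- Design effect: DE = 1 + (8.6 − 1) × ICC
- Variance ratio of the arm difference: R = (1 + DE)/2
- Power of a test with a valid standard error: Φ(0.23/(0.0818 × √R) − 1.96)
- True two-sided error of a test that ignores clustering: 2 × [1 − Φ(1.96/√R)]
- Effect detectable with 80% power: 2.8016 × 0.0818 × √R

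| ICC | DE | R | √R | Power at 0.23 | Type I error if ignored | Detectable effect |
|---|---|---|---|---|---|---|
| 0 | 1.000 | 1.000 | 1.000 | 80.3% | 5.0% | 0.229 |
| 0.01 | 1.076 | 1.038 | 1.019 | 78.8% | 5.4% | 0.233 |
| 0.02 | 1.152 | 1.076 | 1.037 | 77.4% | 5.9% | 0.238 |
| 0.05 | 1.380 | 1.190 | 1.091 | 73.2% | 7.2% | 0.250 |

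**Step 4: slack.** Power falls to 80% when √R = 0.23/0.2291, that is R ≈ 1.0076. This gives ICC = 2 × 0.0076/7.6 ≈ 0.002.

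**Step 5: group size.** At ICC 0.05, power is 75.5% with 6 analysed per group and 70.9% with 11.25 (15 × 0.75).

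**The case against.** **The model is given in one sentence of a condensed article.** Random effects, covariance structure and degrees of freedom are commonly left to the analysis plan, which is not shown. A reader might infer that the protocol declares participants independent across session groups. It does not say so; it names two factors and is silent on the rest. This objection stands against that reading. It does not reach the sample size, which is fixed without an allowance and which an analysis plan cannot change. Nor does it alter the fact that the model, followed as written, omits the grouping.

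**The ICC may be very small.** At 0.01 the power loss is about 1.5 points and the standard error grows by 2%. That stands, and it is why the size is uncertain. The article gives no ground for assuming a negligible value, and its emphasis on group support points the other way.

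**Type I inflation needs a further condition.** If the sessions change nothing for anyone, they create no correlation. Inflation arises only if groups or facilitators differ while the average effect is zero. That is possible but not certain, so the error rates above are conditional.

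**The 80% concerns one outcome.** It applies to diastolic blood pressure at 0.23, and the article expects larger effects for weight, waist, glucose and lipids. At ICC 0.05 an outcome with a true effect of 0.25 still has 80% power. This answers the power point for such outcomes but not the interval width, which does not depend on effect size.

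**Recruitment was well short.** By 15 November 2012, 266 people were randomized, with recruitment expected to end in February 2013. Power at 299 per arm may describe a sample never reached. The standard-error problem remains at any size. If half of the 266 are in the intervention arm, there are about 133/11.5 ≈ 12 session groups, few enough for the degrees of freedom to matter.

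**Conclusion.** The point holds conditionally. The stated sample size is an independent-individuals calculation with almost no slack, and the stated model omits the session group. For any positive ICC the standard error of the arm difference is understated; above an ICC of about 0.002, power for a 0.23 effect falls below 80%. Over ICC 0.01 to 0.05 with about 8.6 analysed per group, the standard error is understated by a factor of 1.02 to 1.09 and power is 78.8% to 73.2%. If group effects also vary under the null, the true error is 5.4% to 7.2%.

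A reader might go further and conclude that the test is certainly anti-conservative, that every primary outcome is underpowered, or that power drops to around 60%. The documents support none of these. Inflation needs between-group variation under the null, the power claim is tied to the 0.23 effect, and a loss that large needs an ICC near 0.10 at the enrolment group size, for which the article offers no basis.

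The change should be made but is not essential to the trial's validity, because its size rests on an assumed ICC. Shared facilitators across groups could add correlation that is not counted here.

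**What to change.** **Data analysis.** Add a random effect for session group in the intervention arm only: a partially nested mixed model with each control treated as a singleton, residual variance allowed to differ by arm, and small-sample degrees of freedom (Kenward-Roger or Satterthwaite). Include facilitator as a further level in a sensitivity analysis.

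**Sample size and power calculation.** State that 299 per arm assumes independence. Restate power for the 0.23 effect over ICC 0.01 to 0.05 at the expected analysed group size, as in the table above. No additional enrolment is proposed.

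**Cost.** The analysis file needs identifiers for session group and facilitator, which the trial should already hold. No participant procedure changes. Intervals become slightly wider and the stated power slightly lower.
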